## Abstract

Supplemental Digital Content is available in the text

## Introduction

1

Since 1999, medical errors (MEs) have been recognized as a leading source of mortality in patients.^[1]^ Recent reports suggest that as many as 250,000 to 400,000 patients die each year in the United States as a result of MEs and that millions of preventable injuries occur per year due to MEs.^[2]^ MEs have been defined as unintended acts in the process of care, either omission or commission, or acts that do not achieve their intended outcome.^[3,4]^ Most MEs do not result in harm to the patient, but a proportion of them causes harm^[5,6]^; these MEs are called preventable adverse events (AEs) – injuries or damages resulting from a medical intervention or omission of an intervention. Consequences of AEs vary in severity, from treatment modifications to contributing to death.^[2,5,7]^

Common risk factors for AEs are invasive procedures, long hospital stays^[8–11]^ and organizational factors such as professionals’ turnover, night/day shifts, and complex transmissions.^[12,13]^

Neonates hospitalized in neonatal intensive care units (NICUs) are at high risk of ME-related damage. In this population, rates of AEs vary by degree of prematurity: the risk of AEs is 57% for extremely low-gestational-age (GA) neonates born before 28 weeks’ GA (ELGANs) as compared with 3% for term newborns.^[9]^ Supplementary risk factors in the ELGAN subgroup are clinical fragility due to low weight, overall immaturity and inability to compensate for clinical alterations as well as complex care (catheters, tubes, artificial ventilation) and types of medications needed.^[9,14–21]^ In addition, neonatal-specific AEs described include identification errors among multiple-birth infants,^[22]^ breast milk errors,^[21]^ skin lesions due to immaturity^[9,15]^ and nasal injuries from non-invasive ventilation.^[23]^ Finally, hospital-acquired infections (HAIs), especially central-line-associated bloodstream infections (CLABSIs) are a leading cause of mortality and neurological morbidity in premature neonates^[23–25]^ which can be reduced by adherence to appropriate infection control measures.^[26,27]^

Various strategies exist to measure patient safety in clinical settings. To measure MEs and AEs rates over time, trigger-based retrospective chart reviews (RCRs) are the method of choice. These systematic medical-record surveillance methods are sensitive and reliable, detecting AEs at 10-fold higher rates than administrative screening tools and hospital reporting systems.^[28,29]^ Voluntary and anonymous occurrence reports by healthcare professionals (HCPs; nurse, resident or physician) may help identify MEs and near misses but are unreliable to measure the evolution of ME and AE rates over time because they depend on HCPs’ perseverance and regularity to collect them exhaustively, and HCPs may miss some MEs and AEs such as HAIs.^[28–30]^

In the last decades, patient safety efforts have focused on harm rather than error.^[31]^ However, the results of studies are disappointing, because reducing AE rates seems difficult to achieve.^[5,32]^ Besides checklists^[33]^ and bundles^[34]^ to prevent some types of HAI, a common approach to prevent the recurrence of AEs is to proceed to a review of care, such as root cause analysis (RCA), an analysis of triggers by a sentinel event that resulted in damage (physical or psychological injury) or death. RCA aims at identifying the cause(s) that underlie variations in performance and thus improving the systems and processes to decrease the odds of an event.^[35]^ Since the 1990s, various RCA approaches have been used, and the lack of standardization of these methods has resulted in a variation in the quality and comprehensiveness of the outcomes. In the last years, some problems have been described with RCA,^[36]^ as well as a lack of strong evidence to support its effectiveness in improving safety in medical settings.^[37–40]^

This study aims to evaluate the impact of combined multi-professional education on the rate of AEs in NICUs. This program combines education in a standardized RCA-like method^[41]^ and the creation of bundles (insertion bundle, daily goals bundle, maintenance bundle) to prevent late-onset neonatal central-line-associated bloodstream infection. The outcome is measured by RCR based on a preexisting specific NICU trigger tool method.^[42]^

This is a stepped-wedge cluster randomised trial (SW-CRT) with trigger-based RCR measurement of AE rates in neonates hospitalized in NICUs. The stepped-wedge design relies on the sequential implementation of the experimental intervention within all participating units during subsequent periods and in a randomized order.^[43,44]^ In contrast to more conventional parallel-group cluster randomized trials, all clusters will benefit at some point from the intervention of interest, thus accumulating information both during a pre- and post-interventional period (each cluster being its own control). Two main situations typically justify the use of a stepped-wedge design: firstly, cases in which an intervention is deemed globally beneficial with limited drawbacks, ethically justifying its wide implementation in all participating clusters and/or secondly, cases in which organizational, logistical or financial reasons preclude immediate and simultaneous implementation in all units randomized to the experimental group. For the present trial, the following elements supported the decision to use a stepped-wedge design: interest of the intervention potentially beneficial for all centres; practical interest of the progressive implementation of the intervention; statistical interest related to a potentially more effective control of intra-cluster correlation allowing, under certain conditions, a statistical power greater than that of conventional cluster trials at equivalent numbers of people^[45]^; interest in monitoring over time the persistence of the expected benefit and to detect possible underlying “natural” temporal trends; and interest in obtaining balance in cluster characteristics after randomization, in particular when the number of clusters is low.

## Methods and analysis

2

### Study design

2.1

This is an SW-CRT. The study diagram (Fig. 1) presents the timing of the interventions and the steps per cluster.

**Figure 1 F1:**
[figure not shown]
Diagram of the timing of the intervention in the SEPREVEN stepped-wedge cluster randomised controlled trial. The trial lasts 20 months (M) per participating unit. Each randomization cluster (C) C1, C2 and C3 comprises 4 units. Intervention is implemented within each randomization cluster following a random sequence. The gray cells represent the (pre-educational) *control* periods, blue cells a 4-months *transition* phase and orange cells the (post-educational) *intervention* periods. The transition phase allows for the time to integrate the program into the units. During this *transition* period the unit is not in a *control* or *intervention* phase and does not contribute to primary endpoint analysis.

Sample selection: Study population and setting

Patient eligibility criteria

Inclusion criteria: All patients will be included as follows:

-In hospital during the 20-month study period between November 23, 2015 and November 2, 2017 (inclusion start dates varying by unit) in one of the 12 participating units,-Corrected GA ≤ 42 weeks (≤42 weeks + 6 days) at the time of admission,-Hospitalization period is longer than 2 calendar days,-Parents have been informed and will not oppose the use of their newborn's data.

### Participating units’ eligibility criteria

2.2

The following criteria were considered to include hospitals in this study: NICUs should exclusively be dedicated to newborn care (no pediatric ICU); should not have planned to implement a new ordering program; and for feasibility reasons and external validity, 6 hospitals should be located in Ile de France (Paris area) and 6 in distinct regions in France.

### Recruitment of patients

2.3

The investigators at each site will be responsible for including all the patients who meet the inclusion criteria. The study will be proposed to parents, and the information note signed by the investigating doctor will be delivered to them; another copy will be kept by the investigator for 15 years. To optimize recruitment in this routine care study, the information letter will be delivered to parents by the HCP usually in charge of patient care. In the absence of parental opposition, the infant will be included in the study.

### Randomization and allocation concealment

2.4

Randomization will be performed at the unit-level (no randomization oat the patient level). Before the trial starts, the units will be randomized to one of the 3 sequences (4 units/cluster, see Fig. 1) by use of a computer-generated list, without pre-specified characteristics. Each cluster will receive the intervention at different times: therefore, the total duration of the 3 periods will not be the same for the 12 units. Time blocks of 4 months will be considered, including the individual control and intervention periods as well as the transient phase.

### Intervention

2.5

The program itself consists of 3 educational actions to be implemented during the 4-month “transition” period.

At the local unit-based level, 3 actions will take place:

First, it will consist of training in the ORION standardized RCA method, derived from aeronautics and adapted for several years to care.^[41]^ This method allows local HCPs to perform an RCA in a simple way in their NICU setting. At the beginning of the intervention period, local HCPs (NICU senior physicians and nurses, optionally a risk manager, maximum 13 persons) will be trained in situ for 1 day to conduct a feedback meeting and perform a systemic analysis of risky events. Following this training, the RCA will be implemented from the transient phase on; each of the RCAs will consist of a chronological reconstruction of the facts, leading to the collective identification of one or more barrier actions to be implemented and a verification of the effective implementation of the actions decided in the preceding RCA. This training will be delivered once; a second 4-hour training will be implemented if asked by the unit. The training is meant to be used during the months following the transient phase.

Second, the intervention will include training for each unit in preventing central-line-associated bacteraemia with the participation of a local senior NICU physician and nurses involved in patient care: each unit will create bundles (insertion bundle, daily goals bundle, maintenance bundle) according to the rules of good practice for central venous catheters promoted internationally,^[26]^ with a possible adaptation to specific local practices. These bundles are meant to be used continuously during the intervention period.

Third, a poster created for the study will present the drugs and solutions at risk of necrosis in the event of extravasation through the peripheral venous route. This poster is meant to be used continuously during the intervention period.

The anticipated effect of this multifaceted intervention is a mixture of immediate and delayed effects: for the RCA education, a delayed but sustained effect regarding various AEs, and for bundles and the extravasation poster, an immediate and sustained effect.

At the cluster level, 2 telephone meetings will be held by the investigator (LC) during the transition phase, as well as guidance and follow-up of the creation of bundles.

### Outcomes

2.6

#### Primary endpoint and primary outcome measure

2.6.1

The primary objective of the study is the effectiveness of a multiprofessional training program for reducing the rate of AEs measured by RCR with a NICU trigger tool. The corresponding primary endpoint will be the rate of AEs/1000 patient-days in the NICU, compared between control and intervention (post-educational) periods with the SW-CRT design.

#### Secondary endpoints and secondary outcome measures

2.6.2

1.Rates of preventable AEs/1000 patient-days. Assessment of the effectiveness of the intervention in reducing the rates of preventable AEs (number of AEs/1000 patient-days) measured by RCR.2.Rates of severe and non-severe AEs/1000 patient-days.^[46]^ Assessment of the effectiveness of the intervention in reducing the rates of severe and non-severe AEs (number of severe and non-severe AEs/1000 patient-days) measured by RCR.3.Rates of CLABSIs/1000 patient-days and /1000 catheter-days. Assessment of the effectiveness of the intervention in reducing the rates of CLABSIs measured by RCR.4.Rates of HAIs/1000 patient-days. Assessment of the effectiveness of the intervention in reducing the rates of HAIs measured by RCR.5.Rates of unprogrammed extubations requiring reintubation/1000 patients-days and /100 ventilator days and /100 hours. Assessment of the effectiveness of the intervention in reducing the rates of these unplanned extubations measured by RCR.6.Rates of medication errors/1000 patient-days. Assessment of the effectiveness of the intervention in reducing the rates of medication errors measured by RCR.7.Description of types and severity of MEs and AEs occurring in NICU patients with a prospective rating of severity of outcome after the AE occurred by using the National Coordinating Council for Medication Error Reporting and Prevention (NCCMERP) classification index. Description will be based on routine care occurrence reports by HCPs for the entire study population.8.Economic impact measured by using the entire study population's clinical data and outcome criteria and impact of the intervention measured by using the RCR population's clinical data and outcome criteria.9.Health-related outcomes impact of the study (measured by using the entire study population’ outcome criteria) and impact of the intervention (measured by using the RCR population's outcome criteria).10.Description of severe extravasation injuries and evolution (context and rate per patients).11.Description of bacterial species collected from blood culture specimens: genotype, phenotype and resistance to antimicrobial and antiseptic agents

For units participating in these secondary objectives:

11.Prospective dermatitis score before and after the use of antiseptic for central line insertion in premature neonates born before 32 weeks’ GA and <15 days old.12.Description of nasal scores during the use of non-invasive nasal ventilation in premature neonates born before 32 weeks’ GA.13.HCPs’ attitude regarding AE disclosures to parents. Description of characteristics of disclosed and undisclosed AEs, HCPs’ motivations, and perceived parental reactions. Description will be based on a prospective self-administered questionnaire for HCPs for each routine care occurrence report.14.Impact of the number of nurses and patients present in the NICU on rates of AEs. Prospective collection of the number of nurses and number of patients according to their level of care.15.Impact of each unit's preexisting safety culture on the impact of the intervention.

### Data collection

2.7

#### Record-review process for the primary endpoint

2.7.1

This part of the data collection will start during 2018, after the end of the patients’ inclusion period, and will imply to involve external reviewers, not present in the prior steps of the trial.

Record reviews (RCRs) will be conducted by using the NICU-specific trigger tool.^[42]^ It will be applied according to the procedure described in the NICU Trigger Toolkit^[47]^ translated into French by our research team for the purpose of this study. This NICU trigger tool consists of 14 triggers or clues that indicate the possibility of AE-induced harm. According to this method, when the examiner finds a trigger, she/he examines the record further to determine whether the injury apparently resulted from an AE. As mentioned in the NICU Trigger Toolkit, AEs identified via sources other than the trigger are also considered. To capture only AEs related to the participating NICU, AEs already present on admission and infections occurring before day 2 after admission to the unit will not be considered AEs. For each record, the reviewers will complete a table corresponding to the triggers found and the potential AEs. With an additional document, they will record on an AE collection form the standardized information for each identified potential AE (name, preventability, NCCMERP-graded severity^[46]^ occurrence date, comment, associated triggers). All potential AEs and associated characteristics will be confirmed or not by a physician reviewer.

#### Routine care occurrence reports over the 20-month period

2.7.2

This part of the data collection will take place prospectively during the 20-month inclusion period. A routine voluntary multiprofessional reporting of MEs and consequence will take place to identify MEs and AEs. Routine nasal injury scores and skin scores will also be completed during this entire period. HAIs will be recorded by a NICU physician on dedicated forms. The disclosure procedures for communicating the MEs and AEs to parents will be detailed in an additional form in the units participating in this study component.

#### AE characterization: severity and preventability

2.7.3

The NCCMERP classification index will be used to rate the severity of the MEs and AEs.^[46]^ This index has the advantage of standardizing the damage severity classification, thus allowing to compare data from studies. According to this classification, lower-severity harms are defined as category E and higher-severity harms as categories F, G, H or I. This index will be used for the routine care occurrence reports and for the severity grading of RCR AEs.

Preventable AEs will be defined as any event that could have been avoided by an appropriate error management strategy.^[48]^ According to these proposals, HAIs, most MEs and unplanned extubations would be considered preventable. Other AEs such as skin lesions or nasal injuries would need an individual assessment to determine preventability. In case of uncertainty regarding an AE's severity and/or preventability, an expert neonatologist committee, blinded to the AE's occurrence period, will be asked to conclude.

#### Other characteristics

2.7.4

Demographic data (birth date, sex, multiple gestation, etc.), medical data (gestational age at birth, birth weight, ventilation, central lines, etc.), and outcomes (mortality and specific outcomes) as well as ME and AE data (nature, severity of consequences, communication) and HAI data (dates, antibacterial treatment duration, data on blood cultures and local bacterial specimens) will be collected for all patients.

### Statistical analysis plan

2.8

#### Sample size and power calculation

2.8.1

The primary endpoint is the rate of AEs/1000 patient-days (hospitalization days). Analysis of available data from the literature as well as our own unpublished routine data allowed for anticipating an average basal value of 60 AEs/1000 patient-days in the absence of any intervention. The calculation of the required sample size was based on the Poisson distribution to compare control and intervention AE rates. To do so, calculations were performed according to Hemming and Girling,^[49]^ derived from the initial approach by Hussey and Hughes,^[50]^ to take into account the effect of the stepped wedge (or design effect) study specification on the sample size calculation.

Considering a total number of 12 units divided into 3 randomization clusters over 5 study periods, a 5% two-tailed alpha risk and an intraclass correlation coefficient ranging from 0.01 to 0.1, we will need to include 15 patients per unit per month (i.e., 15 × 4 = 60 patients per cluster per 4-month evaluation period), for a total of 15 × 20 × 12 = 3600 patients over the study period, a cumulative 61,200 to 72,000 patient-days corresponding to an expected mean hospitalization length from 17 to 20 days) to show, with a power of 80%, a minimum relative reduction of 17% in rates of AEs (i.e., a decrease from 60 [control] to 50 [intervention] AEs/1000 patient-days).

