#### Outcomes measured

2.8.3

The effectiveness of the intervention will be measured by RCR of files selected by drawing lots. As previously mentioned, this analysis will involve using the NICU trigger tool developed and described by Paul Sharek.^[42,47]^ Fifteen files/month/unit will be drawn at random from the pool of all patient files included in the study, for each of the 20 months of participation. Only the part of the file corresponding to the stay in the unit participating in SEPREVEN will be considered. AEs will be assigned to the control or intervention period according to their date of occurrence.

The records will be analyzed by reviewers external to the unit and to the promotor, educated in the RCR for the study purpose. The reviewers will be unaware of the study intervention and clusters. The analysis will be made progressively in alphabetical order of identification code, thus mixing files from the different periods. To limit internal incoherence in analysis, the same reviewer will analyze all charts from a same unit. Each suspected AE will have to be confirmed by a physician educated in the RCR and unaware of the patients’ dates of stay, in agreement with the external reviewer. In the event of disagreement between the reviewer and the physician about the presence, name, severity or preventability of the AE, the case will be discussed with a third physician and consensus will be sought.

Once validated, the trigger-tool data and AE data will be entered in the e-CRF.

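### The stated 80% power for a 17% reduction does not allow for the transition blocks that the primary analysis leaves out; with them excluded, power is roughly 40 to 60%

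*Protocol article*

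**What the plan says.** Section 2.8.1 takes 12 units in three randomization clusters (sequences) over five periods, "a 5% two-tailed alpha risk" and an intraclass correlation of 0.01 to 0.1. It needs 15 patients per unit per month, "for a total of 15 × 20 × 12 = 3600 patients over the study period", or 61,200 to 72,000 patient-days at a mean stay of 17 to 20 days. The stated purpose of this number is "to show, with a power of 80%, a minimum relative reduction of 17% in rates of AEs", that is, "a decrease from 60 [control] to 50 [intervention] AEs/1000 patient-days". On method it says "The calculation of the required sample size was based on the Poisson distribution", with a stepped-wedge adjustment "derived from the initial approach by Hussey and Hughes".

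The Figure 1 caption (section 2.1) describes a 4-month transition in each unit. During it the unit is in neither a control nor an intervention "phase and does not contribute to primary endpoint analysis". Section 2.4 places this phase within the 4-month time blocks. Section 2.8.3 has the charts sampled across the whole period: "Fifteen files/month/unit will be drawn at random from the pool of all patient files included in the study, for each of the 20 months". It also assigns each adverse event to a period by its date. Section 2.8.2 specifies a mixed-effects Poisson model with a fixed time term and a random unit effect.

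**The concern.** The patient total in 2.8.1 counts every month of every unit, while the caption removes one block in five from the primary comparison. Nothing in 2.8.1 allows for the removal.

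The loss is more than a fifth of the data. In a stepped-wedge trial adjusted for time, the effect is identified largely by units that are in different conditions at the same time. The transition block sits exactly at the switch, so emptying it removes most of that concurrent contrast.

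At stake is how the result is read. A null finding would be set against a claimed 80% power for a 17% reduction that the analysed design does not have. The estimator, its type I error and the validity of the effect estimate are not affected.

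**Working it through.** **Inputs.** From 2.8.1: rates 0.060 and 0.050 per patient-day; stay L = 17 to 20 days; ICC 0.01 to 0.1; 15 × 4 = 60 charts per unit-block; 12 units, four per sequence; two-sided 5%. From the Figure 1 caption and 2.4: a one-block transition inside five 4-month blocks. Assumption: blocks are aligned across units.

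**Layout.** With three sequences, five blocks, control before the transition and intervention after it, the transition must fall in blocks 2, 3 and 4 (C control, T transition, I intervention):

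- Sequence 1: C T I I I
- Sequence 2: C C T I I
- Sequence 3: C C C T I

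Only block 3 contains both control units (sequence 3) and intervention units (sequence 1).

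**Analysed data.** 15 × 16 × 12 = 2880 charts; 2880 × 17 = 48,960 and 2880 × 20 = 57,600 patient-days. The difference from 3600 is 720 charts. This is an equivalent: events are assigned by date, so patient-days drop out rather than whole charts.

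**Variance model.** Generalised least squares on unit-block means of events per patient:

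- Poisson variance per patient at the mean rate: s² = 0.055 × L
- cell variance: s²/60
- between-unit variance: τ² = ICC/(1 − ICC) × s²
- difference to detect: d = 0.010 × L
- power = Φ(d/SE − 1.96)

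**Reproducing the stated figure.** Transition treated as analysed data, categorical periods, L = 17, ICC = 0.01: s² = 0.935, cell variance 0.0156, τ² = 0.0094, d = 0.17, SE = 0.0614. Power = Φ(0.17/0.0614 − 1.96) = Φ(0.81) = 0.79. Coding the transition as control or as intervention gives the same result. As a cross-check, the closed-form stepped-wedge design effect with two baseline blocks and three steps, at L = 17 and ICC 0.01, is (3.99/3.09) × 3 × 0.99/(2 × 2.667) = 0.719. The individually randomised total is 2 × 7.849 × (1.02 + 0.85)/0.17² = 1016. Then 1016 × 0.719 × 5 ≈ 3652; at ICC 0.1 the result is 3628. Both are close to the stated 3600.

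**Transition cells empty.** Same case: SE = 0.0983, power = Φ(0.17/0.0983 − 1.96) = Φ(−0.23) = 0.41. A loss of 20% of the data alone would inflate the SE by √1.25, to 0.0686, and give power of about 0.70. The remaining fall comes from the lost concurrent comparison.

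| Power for 60 to 50 per 1000 | L=17, ICC 0.01 | L=17, ICC 0.1 | L=20, ICC 0.01 | L=20, ICC 0.1 |
|---|---|---|---|---|
| Transition counted, categorical periods | 0.79 | 0.75 | 0.85 | 0.82 |
| Transition empty, categorical periods | 0.41 | 0.38 | 0.47 | 0.43 |
| Transition empty, one linear term over blocks | 0.51 | 0.46 | 0.58 | 0.52 |

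**Detectable reduction at 80% power.** (1.96 + 0.8416) × SE/(0.060 × L), with variance held at the 55 per 1000 rate:

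- Categorical: 2.8016 × 0.1067/1.20 = 25% (L = 20, ICC 0.01) to 2.8016 × 0.1036/1.02 = 28% (L = 17, ICC 0.1).
- Linear: 2.8016 × 0.0929/1.20 = 22% to 2.8016 × 0.0916/1.02 = 25%.

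Recomputing the variance at the new mean rate lowers the lower ends slightly, to 24.4% and 21.4%.

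**The case against.** Four points on the other side have weight.

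- **Time coding.** Section 2.8.2 speaks of a single time term, which may mean one trend rather than period indicators. A reader might infer from the categorical result that power is simply 40%, and that the trial is more likely than not to miss its target effect. The documents do not support either statement as a fixed conclusion. With one linear term over blocks, power reaches 0.58; with linear time in months it is 0.51 to 0.63.
- **Staggered starts.** The caption to Figure 1 and the inclusion criteria beside it give a calendar window longer than 20 months, with start dates that differ between units. The statement about block 3 therefore holds in trial time and not necessarily in calendar time. The distribution of starts is not given. If starts are assumed to spread over 0 to 3 months within each sequence, power is 0.45 to 0.56 with categorical months, 0.49 to 0.61 with 4-month calendar blocks and 0.51 to 0.64 with linear months.
- **Origin of the 80%.** A reader might infer that the authors certainly counted the transition charts in the power calculation. Only the patient total shows this openly. A compressed four-period layout with no gap (2880 patients) gives 0.71 to 0.83, so ignoring the gap could also lead to about 80%. That layout, however, contradicts the five periods and 3600 patients in the text.
- **Intent.** Leaving out the transition is a deliberate choice, explained in the caption, and is not itself an error.

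The first three points widen the range. None brings a time-adjusted five-block calculation with empty transition cells up to 80%. Dropping time altogether would give about 99%, but both 2.8.2 and the cited method adjust for time.

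**Conclusion.** The conflict between 2.8.1 and the Figure 1 caption is real, and the 80% figure is not supported for the analysis described. Under aligned blocks and pure Poisson variation, power for 60 to 50 events per 1000 patient-days is about 0.38 to 0.47 with categorical periods and 0.46 to 0.58 with one linear term. Allowing for staggered starts and finer time coding, roughly 40 to 60% is a fair summary. The reduction detectable with 80% power is about 24 to 28% or 22 to 25%, against the stated 17%.

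The loss of contributing patient-days follows directly from the text. The power figures rest on the protocol's inputs and on the Hussey-Hughes variance. Overdispersion, or a unit effect that varies between periods, would lower them further; the documents give no values for either.

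**What to change.** In section 2.8.1:

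1. State the contributing exposure, 48,960 to 57,600 patient-days (the equivalent of about 2880 charts), next to the 3600 charts sampled.
2. Recompute power for 60 to 50 per 1000, and the reduction detectable with 80% power, with each unit's transition cells empty and the actual start dates used.
3. Name the time coding of the primary model (period indicators or a single trend, and its unit), and use the same coding in the calculation.

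The cost is a short recalculation and a less favourable stated power. No change to the intervention, the sampling or the exclusion of the transition is needed for the correction.
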